| 
Initial descriptive analysis will present the profile of the subjects by study arm without using statistical comparisons. For the primary hypothesis, the change in PHQ-9 scores from baseline to week 6 will be compared between groups. A mixed effect model that includes treatment group, time and their interaction as fixed effects, and individual subjects as random effects will be fit using PHQ-9 at all available assessments. A linear contrast will be used to test the difference between groups in changes from baseline to week 6 in PHQ-9 scores. Two tailed tests and significance level of 0.05 will be used. Secondary outcomes will be analysed using analogous mixed effects generalised linear models. Pre-specified subgroup analyses of the primary outcome will be explored by baseline depression severity (severe versus moderate) and duration of depression at baseline split at the median. Differences in AEs by study arm will be compared and presented as proportions as described in Section I. Safety and differences will be assessed using Fisher's exact test.
 
We will conduct an exploratory mediation analysis using methods described by Valeri & Vanderweele to examine whether adherence to the diet, changes in microbiome, and cortisol awakening response appear to mediate changes in depression assessed by PHQ-9. Extracted faecal information will be sequenced to obtain a global representation of the microbiome compositions, and Alpha diversity will be measured using Observed Species, Whole Tree Phylogeny, and Shannon and Simpson indices. Spearman correlations will determine associations between alpha diversity metrics, individual microbes, and PHQ-9 scores. Kruskal–Wallis one-way analysis of variance tests will be performed to compare relative abundance of the top ten genera, with false discovery rate (FDR) corrections between dietary groups.
 
The extent of missing data will be reported descriptively, including the number of missing data in each group, and baseline characteristics of people with and without missing outcome data. The primary analysis, with mixed models, is valid under the assumption that data is missing at random (MAR). The robustness of the conclusions to the MAR assumption will be tested in sensitivity analyses as below –
 
 
1. Sensitivity analysis assuming everyone with missing outcome data has severe depression
 
2. Sensitivity analysis assuming everyone with missing outcome data has no depression (included for completeness, not for plausibility)
 
 |                                         |                             |

3. Repeat main analysis with analysis restricted to (a) those with maximum of one missing observations (b) those with maximum of two missing observations

Complete case analysis will be used as the primary analysis if the proportion of missing data is below 5%. We will conduct a sensitivity analysis to explore reasons for missingness and determine appropriate handling of missing data. The following approaches may be applied based on the missing data: single imputation (e.g., last observation carried forward) and full information maximum likelihood estimation. Intention-to-treat analysis using baseline or last observation carried forward (LOCF) are recommended for parallel group randomised trials by CONSORT guidelines since they provide a full report of any deviation of the intervention and includes every participant who enrolled in the study and completed baseline measures, regardless of whether they completed the intervention. ITT also gives an unbiased estimate of the treatment effect. If data are missing not at random (MNAR) for our continuous dependent outcome variables, full information maximum likelihood estimation will be used because it is more compatible between the imputation and analysis models compared to multiple imputation.

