high in people with depression, which are correlated with depression severity. Recent data found decreased concentrations of pro-inflammatory cytokines in the blood in a ketogenic diet. Fourth, KDs may change the gut microbiome and preliminary evidence suggests that gut microbes modulate brain function, particularly in relation to mood disorders. Studies in rodents have shown that a ketogenic diet reduced alpha-diversity (number of different species) of intestinal microbes but increased the abundance of *Akkermancia muciniphila*, a known SCFA producer, which is associated with improved metabolic health. These studies also demonstrated that the altered gut microbiome was associated with the seizure-reducing effects of the keto-diet, which was more prominent in stressed animals. Monitoring the changes in the gut microbiome following a ketogenic diet regime in people with treatment-resistant depression and correlating the abundance of microbial communities with subjective depression ratings may reveal the mechanisms underlying the potential psychotropic effect of a ketogenic diet. Overall, clarifying the impact of KDs on the microbiome and cortisol and the association with changes in depression would help assess whether this is an important mechanism in the effect of KDs on depression if one is found.

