## 4.7. MULTIPLE COMPARISONS AND MULTIPLICITY

As the comparisons have been pre-specified, we will not correct for multiple testing. The level of statistical significance will be set at  $p < 0.05$ .

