## 7. MECHANISTIC ANALYSES

If results from primary analyses warrant further investigation, a further analysis plan for analyses of mediation and mechanistic variables will be prepared with a view to a further publication.

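### The microbe-to-PHQ-9 Spearman correlations are specified without diet arm, time point, level-or-change choice or false discovery rate control, so a pooled post-baseline analysis would be confounded by arm.

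*Combined protocol and SAP*

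**What the plan says.** Protocol Section J, item 4 (Analysis of Outcome Measures), gives the analysis in a single sentence: "Spearman correlations will determine associations between alpha diversity metrics, individual microbes, and PHQ-9 scores". Arm, baseline value, time point, the choice between level and change, and the list of taxa are all absent.

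False discovery rate control appears only in the next sentence, for Kruskal-Wallis tests that will "compare relative abundance of the top ten genera, with false discovery rate (FDR) corrections between dietary groups".

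The correlation has a stated purpose. Protocol Section E says that "correlating the abundance of microbial communities with subjective depression ratings may reveal the mechanisms underlying the potential psychotropic effect of a ketogenic diet". SAP Table 1 (section 1.4) lists change in the microbiome, over all species, as a mechanistic outcome at baseline and week 6.

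Three other passages bear on the point:

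- Shortly before the correlation sentence, Section J says: "We will conduct an exploratory mediation analysis using methods described by Valeri" and a co-author. Change in the microbiome is one of the candidate mediators.
- SAP section 7 says that, if the primary results warrant it, "a further analysis plan for analyses of mediation and mechanistic variables will be prepared with a view to a further publication". The SAP itself does not mention the Spearman correlations.
- SAP 4.7 says: "As the comparisons have been pre-specified, we will not correct for multiple testing".

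**The concern.** The trial expects the diet to change the gut microbiome and is powered for an effect of the diet on PHQ-9. If both happen and the arms are pooled after baseline, the ketogenic group sits at one end of both distributions and the control group at the other. A correlation then appears for a microbe that has no relation to mood within either arm. Using change scores alone does not remove it, because arm drives both changes.

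At stake is the mechanistic reading. Microbes could be named as candidate mechanisms because the diet moves them, and the stronger the diet's two effects, the more often this would happen. The missing multiplicity control is a second, independent gap. It neither causes nor cures the confounding.

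**Working it through.** **Inputs from the documents.** Difference 5 PHQ-9 points, SD 6, two-sided 5%, 90% power, 32 per group, 35% attrition, 100 to be recruited (protocol Section J, item 3; SAP 2.2). 88 actually randomised (SAP 2.2). Stool at baseline and week 6 only (protocol Table 3; SAP Table 1), so post-baseline means week 6.

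**Inputs assumed, because the documents give none.** The diet's shift of a microbe, d_m, from 0.2 to 1.5 SD; normal distributions within arm; a smaller PHQ-9 effect of 0.5 SD as an alternative; the number of taxa; usable stool from all 88 (44 per arm), with 32 per arm as the lower case.

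**Step 1: the plan's own figure.** d_p = 5/6 = 0.83. A two-sample t-test needs 31.25 per arm, rounded up to 32 (64 in total), with power 0.907. The normal approximation gives 31 per arm. Allowing for attrition, 64/(1 − 0.35) = 98.5, so 99 against the stated 100. The plan's figure reproduces. The plan states no figure for the correlations.

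**Step 2: size of the spurious correlation.** Let the microbe be N(0,1) + d_m × arm and PHQ-9 be N(0,1) − d_p × arm, independent within arm, with equal arms. The expected pooled correlation is

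r = −(d_m × d_p / 4) / √[(1 + d_m²/4)(1 + d_p²/4)].

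For d_m = 1.0 and d_p = 0.83: r = −0.2083 / √(1.25 × 1.1736) = −0.172. On Fisher's scale this is 0.174, with standard error √(1.06/85) = 0.112 at N = 88. The ratio is 1.56, so the chance of p < 0.05 is about Φ(1.56 − 1.96) = 34%.

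**Step 3: simulation.** Pooled Spearman test at 5%, with zero association within arm. The 0.2 SD row comes from 2,000 runs; the others come from 4,000.

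| Microbe shift (assumed) | Mean rho, N = 88 | False positives, 44 per arm, d_p = 0.83 | 32 per arm, d_p = 0.83 | 44 per arm, d_p = 0.5 |
|---|---|---|---|---|
| 0.2 SD | −0.04 | 6% | 7% | 6% |
| 0.5 SD | −0.09 | 14% | 11–12% | 9% |
| 1.0 SD | −0.17 | 37% | 29% | 17% |
| 1.5 SD | −0.24 | 61% | 47% | 29% |

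A fresh run with a different random seed gave 6.5%, 13.5%, 36.1% and 60.6% for the 44-per-arm, 0.83 column. If the diet affects only one of the two variables, the rate stays near 5%.

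**Step 4: the same data with ranks adjusted for arm.** The partial rank correlation rejects in about 4% to 7% of runs in every setting, which is nominal within simulation error.

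**Step 5: multiplicity, with no diet effect at all.** Expected false positives are 0.05 × k. For 100 assumed taxa this is 5, and the chance of at least one, treating tests as independent, is 1 − 0.95^100 = 99.4%. For the four diversity indices plus ten genera, it is 1 − 0.95^14 = 51%.

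**The case against.** The strongest reply is that this sentence is not the trial's mechanistic plan. The protocol calls its statistics section an outline and plans mediation separately. The later SAP omits the correlations and sends mechanistic variables to a further plan. The text does not say that arms are pooled, that week 6 is used, or that levels rather than changes are correlated. A baseline or within-arm correlation would carry no diet effect. Section E says only that correlations may reveal mechanisms.

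Most of this stands, and it limits what can be claimed. The defect is under-specification that permits a biased analysis; a biased analysis has not been expressly chosen. What the reply does not do is correct the sentence. The mediation analysis is a separate item, and nothing says the correlations will be adjusted for arm or kept from mechanistic reading. The further plan is described as still to be prepared, and Section J is the only text on this correlation that it could inherit. It is also conditional on the primary results. If that condition means a PHQ-9 difference, the correlations would be run mainly in the setting that creates the bias.

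A reader might infer three stronger things that the documents do not support:

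- **That any diet effect on both variables will look like a mechanism.** The bias is present whenever both shift, but a 0.2 SD microbe shift raises the error rate only to about 6–7%. The 61% needs an assumed 1.5 SD shift together with the full planning effect on PHQ-9.
- **That SAP 4.7 refuses false discovery rate control here.** That rule sits in the primary-analysis section and concerns pre-specified comparisons. The SAP specifies no microbe correlation, and its section 7 defers such analyses. On this family the documents are silent.
- **That the trial cannot address its mechanistic question.** The mediation analysis is a separate route to it.

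**Conclusion.** The point holds in a limited form. As written, the correlation leaves out arm, time point, level or change, and multiplicity control, while Section E gives it a possible mechanistic reading. On pooled week-6 data with both diet effects present, a microbe unrelated to mood within arm would be declared associated with PHQ-9 in about 6% to 61% of trials at N = 88 and 0.83 SD, against a nominal 5%. At 32 per arm the top of that range is 47%; with a PHQ-9 effect of 0.5 SD it is 29%. Adjustment for arm removes the excess. The missing false discovery rate control is a separate gap, worth about 5 false positives per 100 null taxa.

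These sizes rest on pooling at week 6, which is the natural reading but not stated, and on assumed microbe shifts, normality and number of taxa. The primary analysis is unaffected. This should be corrected before the mechanistic analysis is run.

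**What to change.** In protocol Section J, item 4, and in the further plan promised by SAP section 7:

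1. Replace the plain Spearman correlation with an arm-adjusted rank (partial Spearman) correlation of the baseline-to-week-6 change in each microbe or diversity metric with the change in PHQ-9, accounting for baseline values of both. Show the estimate within each arm beside it.
2. List the taxa and diversity metrics to be tested, or give the rule that selects them, and apply false discovery rate control across that whole family.
3. State that unadjusted pooled correlations will not be read as evidence of mechanism.

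Other arm-adjusted rank methods would serve equally well; what matters is that the choice is fixed in advance. The cost is plan wording and a few lines of code, since stool samples and PHQ-9 are already scheduled at both time points. The downside is fewer nominally significant microbes.

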## Section K. Data management and handling

All information provided by participants is considered **research data** for the purpose of this form. Any research data from which participants can be identified is known as **personal data**; any personal data which is sensitive is considered **special category data**.

Management of personal data, either directly or via a third party, must comply with the requirements of the UK General Data Protection Regulation (GDPR) and the Data Protection Act 2018, as set out in the [University's Guidance on Data Protection and Research](#). In answering the questions below, please also consider the points raised in the [Data Protection Checklist](#) and whether, for higher-risk data processing, a separate [Data Protection Impact Assessment](#) may also be required for the research. Advice on research data management and security is available from [Research Data Oxford](#) and your local IT department. Advice on data protection is available from the [Information Compliance team](#).

### 1. Please mark 'X' against the data you will collect for your research

|                                                                                                                                    |                                     |                                                                           |                                     |
|------------------------------------------------------------------------------------------------------------------------------------|-------------------------------------|---------------------------------------------------------------------------|-------------------------------------|
| Screening documents                                                                                                                |  | Audio recordings                                                          |  |
| Consent records including participant name or other identifiers (e.g. written consent forms, audio-recorded consent, assent forms) |  | Video recordings                                                          |             |
| Consent obtained anonymously (e.g. via online survey)                                                              |  | Transcript of audio/video recordings                                      |  |
| Opt-out forms                                                                                                                      |             | Photographs                                                               |             |
| Contact details for the purpose of this research only                                                                              |  | Information about the health of the participant (including mental health) |  |
| Contact details for future use ( guidance )                                                                        |  | Physiological test results / measurements                                 |             |
| Task results (e.g. questionnaires, diary completion)                                                                               |  | Scans (e.g. MRI, Ultrasound)                                              |             |

|                                                    |                          |                                                                                                            |                                     |
|----------------------------------------------------|--------------------------|------------------------------------------------------------------------------------------------------------|-------------------------------------|
| Data already in the public domain.                 |  | IP addresses (refer to Best Practice Guidance 09: Data collection, protection and management for guidance) |             |
| Specify the source of the data:                    |                          |                                                                                                            |                                     |
| Previously collected (secondary) data              |  | Other (please specify below)                                                                               |  |
| Bank (or other) details required for reimbursement |  | Data generated from Biological samples                                                              |                                     |

**2. How and where will each type of data be stored whilst the research is ongoing (until the end of all participant involvement)?**

List each type of data selected above, and explain how each will be physically transferred (including movement/sharing of audio files, paper records, electronic downloads etc.) from where it is collected to a suitable storage site (e.g. [Nexus365](#) [OneDrive for Business](#), [SharePoint](#), [University servers](#)). State the storage location for each.

Refer to Best Practice Guidance on data collection, protection and management ([BPG09](#)).

**Screening documents:** Participants will be anonymously consenting to the eligibility process in the beginning. The screening will take place online on a secure encrypted online platform (the study eCRF). Screen failures will not be allowed to go through the eligibility assessment again, as the system will recognise the IP address and block any other attempt. This safeguards people who cannot be enrolled in the study for safety reasons due to exclusion criteria they might meet. This anonymous data will be analysed as part of the CONSORT flow chart and kept for 3 years, as the other data.

**Consent records:** Only if potential participants pass the initial screening process will they be asked to complete the full consent form for the study and then give us their name and contact details. This can generate a PDF consent form to be downloaded by the participant. The consent forms will be securely stored in a password-protected study folder on the university's secure and encrypted drive. After being downloaded from the encrypted online platform, they will be retained for a period of 3 years following the completion of the study. Any video recordings will be deleted at the end of the study.

**Contact details for the purpose of this research only:** The research team will use participant contact details to contact individuals about the research study and make sure that relevant information about the study is recorded for participant care, and to oversee the quality of the study. We will also collect and store GP contact details to send one letter at baseline after randomisation and another providing a summary of the participant's progress in depression and anxiety severity at 12 weeks. Such information will be kept online on the study database server and in the end of the study, in a separate database to the one containing research data, on the secure university drive.

**Contact details for future use:** If participants select this option in the consent form, we will keep their name and contact details (i.e. e-mail, telephone) in a secure separate database for 7 years, to inform them about relevant future studies.

**Questionnaire and task results:** All questionnaire data will be entered onto the online database. For the PILT task, data will be collected online using a task run on the servers of Gorilla online (owned by Cauldron Science Ltd). Participants will link anonymously to the URL of the Gorilla based task. All data stored on the Gorilla server will therefore be anonymous. Gorilla servers are encrypted and are within the EU. At the end of the study, we will download and store the anonymised research data securely at the University of Oxford indefinitely. Data will be transferred to the statistical software for analysis and we will perform validation checks (e.g. range checks).

**Test results:** All test results will be identified by the study ID only and be pseudonymous. They will be provided in spreadsheet format to the study team and deleted from the host laboratory. They will be linked into the analysis database and stored for up to 7 years.

The participants will be identified by a unique study specific number and/or code in this database. The name and any other identifying detail will NOT be included in any database used for data analysis.

**Audio recordings:** The qualitative interviews are planned to be conducted using Microsoft Teams with the video of both participants and interviewer turned off. This is a licensed secure and encrypted software approved by the University of Oxford. This platform also provides the capability to generate transcriptions, forming the foundation for creating a permanent and anonymized record of the interviews. The recording process will commence once verbal consent is obtained from the participants through Microsoft Teams. Subsequently, access to the .mp3 files will be tightly controlled and limited exclusively to the designated research team members tasked with analysing these. These individuals will be the only ones authorised to access the recordings for the purpose of this study.

**Other Information about the health of the participant:** We will collect data on participants' depression and treatment of it, key elements of medical history and demographic data to describe participants in the study. All

|                                                                                                                                                                                                                                                                                                                                                                                                                                                                                                                                                                                                                                                                                                                                                                                                                                                                                                                                                                                                                                                                                                                                                                                                                                         |                                                |                                    |
|-----------------------------------------------------------------------------------------------------------------------------------------------------------------------------------------------------------------------------------------------------------------------------------------------------------------------------------------------------------------------------------------------------------------------------------------------------------------------------------------------------------------------------------------------------------------------------------------------------------------------------------------------------------------------------------------------------------------------------------------------------------------------------------------------------------------------------------------------------------------------------------------------------------------------------------------------------------------------------------------------------------------------------------------------------------------------------------------------------------------------------------------------------------------------------------------------------------------------------------------|------------------------------------------------|------------------------------------|
| 
study data will be entered on to the eCRFs. At the end of the study, we will download, delete from the study database platform and Gorilla server, and store the anonymised research data securely on the University of Oxford network drives. Data will be transferred to the statistical software for analysis and we will perform validation checks (e.g. range checks).
                                                                                                                                                                                                                                                                                                                                                                                                                                                                                                                                                                                                                                                                                                                                                                                                                                                      |                                                |                                    |
| 
3. Will you use a unique participant number on research data instead of participant name?
 
If yes, state whether or not you will retain a list of participant names against numbers (pseudonymisation via a linkage list).
 
Where will the list be stored, and when will it be destroyed?
 
Yes, we will retain a list of participant names against their unique code, using the method of pseudonymisation. This list will be kept in a separate file from all other documents in a secure drive with limited access on a strictly need-to-know basis, using password protection. This linkage will be retained until the end of the study then destroyed.
                                                                                                                                                                                                                                                                                                                                                                                                                                                                                                                |                                                |                                    |
| 
4. Who will have access to the research data?
 
Researchers listed on this form, the SSC, and other trained researchers if deemed necessary (e.g. statisticians) will have access to the research data. Access will be granted to the MS IDREC for the purposes of monitoring and/or audit of the research.
                                                                                                                                                                                                                                                                                                                                                                                                                                                                                                                                                                                                                                                                                                                                                                                                                                                                                                          |                                                |                                    |
| 
5. If research data is to be shared with another organisation, how will it be transferred / disclosed securely?
 
We have no plans to share the data, but we are conscious that sometimes researchers ask for access to the data. We will share anonymised data with bona fide researchers with a clear purpose under a data sharing agreement.
                                                                                                                                                                                                                                                                                                                                                                                                                                                                                                                                                                                                                                                                                                                                                                                                                                                                      |                                                |                                    |
| 
6. When and how will identifiable data be destroyed or deleted?
 
N.B. If any identifiable data will be retained beyond the end of the study and/or indefinitely, please state what data this is, and the reasons for retention (e.g. contact details for future studies; photos used in publication). This must be clearly stated on participant information, and specific consent obtained.
 
Recordings of the interviews will be deleted after analysis but the transcripts kept for 3 years after publication.
 
We will keep consent forms for up to 7 years to ensure that there is a comprehensive and consistent record of participants' agreement to participate in the study. These will then be deleted permanently from the drive.
 
We will keep participants' contact details and their GPs' contact details until the study results are published in order to send them a lay summary, and the separate contact information database will be then deleted permanently from the drive. There will be a separate database with contact details for participants who wish to be contacted for future studies. This will be kept for up to 7 years and then permanently destroyed.
 |                                                |                                    |
| 
7. Please confirm that you will store other (non-identifiable) research data safely for at least 3 years after final publication or public release and adhere to any additional research funder policies.
 
For more information about the University policies, please see the University's web pages on research data management.
 
If 'Yes', please give details of who will store the data and on storage format, location and security.
 
If 'No', please provide further details.
                                                                                                                                                                                                                                                                                                                                                                                                                                                                                                                                                                                                                                                                       | 
Yes 
 | 
No 
 |
| 
The final database and the qualitative interview transcripts will have identifying information removed and only these versions will be kept indefinitely in a safe drive with strict-access by the study team on a need-to-know basis. In case a research team requests this database in the future for research purposes (e.g. an individual participant data meta-analysis), each request will be reviewed by the PI and only after establishing a data-sharing agreement between the universities/teams.
                                                                                                                                                                                                                                                                                                                                                                                                                                                                                                                                                                                                                                                                                                                      |                                                |                                    |

